### **Differences in AE rates between HIV+ and HIV- individuals**

A few studies have been completed to assess the differences in AE rates between HIV+ and HIV- individuals. One large study has been conducted in Rakai Uganda that included HIV+ and HIV- men. It used the sleeve circumcision procedure and only enrolled HIV+ men with a CD4 count greater than 350. It found no difference in the AE rate comparing HIV+ to HIV- men overall, but did find that HIV+ men had a higher probability of having wound dehiscence [[10](#_ENREF_10)]. A second study conducted in Kenya also found no association, but this was a secondary analysis and was underpowered [[11](#_ENREF_11)] .

Details:

The Ugandan study enrolled 2,326 HIV- and 420 HIV+ men. It included follow-up visits with active surveillance: visits were done at 24-48 hours, 5-9 days and 4-6 weeks with over 90% of men attended the 4-6 week visit. 6% of HIV+ men and 7.4% of HIV- men experienced at least one AE. Including only moderate and severe AEs, 3.1% of HIV+ men and 3.5% of HIV- men had a moderate or severe AE. Wound dehiscence was more common among HIV+ than HIV- men (2.6% to 1.3%) although they did not adjust for multiple comparisons (p=0.04). They calculated adjusted odds ratios to control for possible confounders, and found that HIV+ men had a 21% reduction in the odds of any AE and a 9% reduction in the odds of a moderate or severe AE compared to HIV- men [[10](#_ENREF_10)]. In a recent follow-up study of a subset of men from the same study to determine whether it was necessary to collect CD4 prior to MC, among 242 HIV + men , AE rates of 0.79 for those with CD4 >350, 1.19 for those with CD4 < 350 (p=.214) [[12](#_ENREF_12)]. They determined that pre-surgical CD4 count was unnecessary for safety.

The second study [[11](#_ENREF_11)] used the forceps-guided method, was conducted in Kenya, and had two arms: one with passive surveillance and one with active surveillance. Their main comparison was AE rates in the active and passive surveillance groups, but they enrolled a total of 119 HIV+ men across the two arms, so they did a secondary analysis of AE rates across HIV-status. They found that in the passive surveillance group, HIV+ men had 1.3-times (95%CI: 0.41-4-4) the odds of an AE while in the active surveillance group those who were HIV+ had 0.61 (0.15-2.6) times the odds of an AE. Since this was an underpowered secondary analysis with small sample sizes of HIV+ men, the odds rations have large confidence intervals and little can be concluded from this publication [[11](#_ENREF_11)] .

In summary, there is growing evidence to support the safety of surgical VMMC in HIV+ men; including those at more advanced stages of disease, however this has not been confirmed with the PrePex device.

### **MC benefits for HIV+ men and their partners**

Male circumcision has been shown to reduce the risk of acquiring other STIs besides HIV. It is well established that MC is associated with reduced prevalence of HPV infection among HIV- individuals, and there is evidence linking MC with decreased HPV incidence among both HIV- and HIV+ individuals [[13](#_ENREF_13)] [[14](#_ENREF_14)] [[15](#_ENREF_15)] . A study of HIV+ men failed to find an association between MC and reduced HPV transmission to their female partners [[16](#_ENREF_16)] , although female partners might still benefit indirectly from their partners’ reduced risk of HPV acquisition. A large RCT involving 5,534 HIV-negative men with 24 months of follow-up found that male circumcision was associated with reduced risk of incident HPV and HSV-2, but not syphilis [[17](#_ENREF_17)] .

Details:

A meta-analysis of observational studies [[13](#_ENREF_13)] found that circumcised men were less likely to have prevalent genital HPV infection that uncircumcised men (OR = 0.57, 95% CI 0.45-0.71). It also found “weak evidence” that circumcision was associated with decreased HPV incidence (RR = 0.75, 95% CI 0.37-0.60). These studies were among HIV- men.

In a Ugandan study among HIV+ men, the researchers found that MC significantly reduced the incidence and prevalence of multiple high-risk-HPV and low-risk- HPV infections. (RR = 0.53, 95% CI, 0.33-0.83) [[14](#_ENREF_14)]

An RCT in South Africa found that the prevalence of high-risk HPV among men who received MC was 14.8% (94/637) compared to 22.3% (140/627) among controls, with a PRR of 0.66 (95% CI 0.51-0.86). This was the first RCT to show a reduction in the prevalence of urethral high-risk HPV infection after MC [[15](#_ENREF_15)] .

A study in Uganda tested female partners of HIV+ men with CD4 count greater than 350 who received MC either immediately or after 2 years. 211 women were in relationships with men in the MC arm and 171 women were in relationships with men in the control group. During 2 years of follow-up, no association with incidence of HPV was detected (IRR = 1.05, 95% CI 0.77-1.43) [[17](#_ENREF_17)]

A large RCT in Uganda enrolled 5,534 HIV-negative uncircumcised men and randomized them to received MC immediately or in 2 years (controls). Their primary outcomes were new HPV, HSV-2 and syphilis infections. Men were followed for two years. The study found that male circumcision was associated with reduced risk of HPV (RR = 0.65, 95% CI 0.46 to 0.90) and HSV-2 (HR = 0.72, 95% CI 0.56 to 0.92) but not syphilis (HR = 1.10, 95% CI 0.75 to 1.65) [[16](#_ENREF_16)] .

### **Do HIV+ men commonly initiate sexual activity before wound healing?**

There is a lack of data on how frequently HIV+ men resume sexually activity before wound-healing. Two studies have some data to address this question and they found that 1.1% and 15.7% of men initiated sexually activity before wound-healing [[10](#_ENREF_10)] [[18](#_ENREF_18)]. Because of the methodologies used, the 1.1% estimate should be viewed as an under-estimate and the 15.7% should be viewed as an over-estimate. Both studies have significant limitations described below. An additional study, also in Rakai, did find that female partners of HIV+ men who resumed sex prior to wound healing had a higher rate of HIV acquisition with 5 of 18 women seroconverting (IRR = 3.50, 95% CI, 1.14-10.76) [[8](#_ENREF_8)].

Details:

A study in Uganda found that 15.7% (66/420) of HIV+ men self-reported initiation of sexually activity before wound-healing was certified as healed. This rate was higher among married men (27.8%). But follow-up, and thus certification of wound-healing, was only done at 24-48 hours, 5-9 days and 4-6 weeks, so this is an over-estimation [[10](#_ENREF_10)].A second study in the same site in Uganda found that 5.5% (10/183) HIV+ men had resumed sexual activity before their week 4 follow-up visit but had not completed would healing during that visit [[18](#_ENREF_18)] .A third study from the site enrolled only HIV+ men age 15-49 who were not stage 3 or 4 and did not have a CD4 count <350[[8](#_ENREF_8)]

### **Time until wound healing**

Three studies looked at time until wound healing comparing HIV+ and HIV- men. Two out of three studies examining men with CD4 counts < 350 found that a smaller proportion of HIV+ men with CD4 count less than 350 had healed by week 4 compared to HIV- men but did not find significant overall differences in healing time between HIV-positive and HIV-negative men . One out of three studies examining only men with CD4 counts >350 found that HIV+ men with CD4 count greater than 350 had slower healing time, and in that study they used the sleeve method. Because the study that found an association between HIV+ men and healing time had the largest sample size of the three studies, and all three studies used different MC methods, it is difficult to make any conclusions.

Details:

A study in Kisumu, Kenya using the forceps-guided method compared the time until healing among men age 18-35 [[19](#_ENREF_19)]. HIV-positive men with signs of Stage 3 HIV or greater were excluded. Men returned weekly to assess if the wound had healed. Comparing 108 HIV+ men to 108 HIV- men, no statistically significant difference in mean time to complete healing was found (33 days for HIV+ vs. 31 days for HIV-). However at week four, 70.4% of HIV- compared to 59.3% of HIV+ men were healed (p=0.09). Among ARV-naïve men, those with CD4 <350 had a mean time to complete healing of 37.1 days compared to those with a CD4 count greater than 31.1 days (p= 0.04). One issue the article raises in the discussion section is that HIV- infection in the first three weeks post-MC is associated with delayed healing, and those individuals should be counseled that they may need to remain abstinent beyond the 42-day period [[19](#_ENREF_19)] .

A study in Uganda using the dorsal slit method compared time until healing among men age 12 and older. 262 HIV- and 177 HIV+ men were enrolled, with participants followed weekly starting at week 3 post-operation. At 4 weeks, 85.9% of HIV- and 77.4% of HIV+ infected men with a CD4 count > 350 and 87.1% of HIV-infected men with a CD4 count less than 350 were healed. The difference between HIV- and HIV+ men with a CD4 count ≥350 was borderline statistically significant (p=0.054). All men in this study had healed by 5 weeks post-surgery [[18](#_ENREF_18)]

A previous study, also in Rakai, Uganda, using the sleeve method enrolled 2,326 HIV- and 420 HIV+ men. They found that at 30 days post-operation, complete wound healing was certified in 73% of HIV+ men and 83.2% of HIV- men (p<0.001), suggesting that HIV- men heal faster. The HIV+ population in this study was restricted to individuals with CD4 count ≥350. 90% of wounds had healed by 6 weeks post-operation [[12](#_ENREF_12)]

In summary, wound healing for those who are HIV+ including those with CD4 <350 does not seem to be very different from those who are HIV-negative.

### **Risks for their partners**

The main risk for partners occurs during the first 6 weeks after MC. One study showed that viral shedding increased during that time, although the increase had subsided in almost all men by six weeks after MC [[20](#_ENREF_20)] . One RCT which attempted to assess whether circumcision in HIV-infected men would reduce transmission of the virus to female sexual partners was stopped early because of futility- 18% of women in the intervention arm and 12% of women in the control arm acquired HIV during follow-up, giving an adjusted HR was 1.49 (0.62-3.57) [[8](#_ENREF_8)]. A meta-analysis of six longitudinal cohort studies also found little evidence that male circumcision directly reduces risk of transmission to women (RR = 0.80, 95% CI 0.53-1.36) [[21](#_ENREF_21)] . With more follow-up time, it is possible that circumcision of HIV+ men is protective for the partner, but there is currently no direct evidence to support this theory.

Details:

A study in Kenya examined penile viral shedding among 20 HIV+, ART-naïve men. Viral shedding generally peaked at week 1, declined steeply in weeks 3-5, and returned to pre-MC levels in week 6. In 28/29 men, no viral shedding was detected after certification of wound healing, so the increased viral shedding was likely due to the local breach in epithelial integrity[[20](#_ENREF_20)].

A RCT of male circumcision in Uganda found no evidence of reduced HIV transmission to female partners. In the study, 922 HIV+ men age 15-49 who were not stage 3 or 4 and did not have a CD4 count <350 men who had uninfected partners were assigned to either immediate or delayed circumcision. Overall, 18% of women in the intervention group (partners in the immediate circumcision group) acquired HIV during follow-up, compared with 12% of women assigned to the control group (partners in the delayed circumcision group). There was no difference in HIV incidence between the circumcised and control groups when the couples waited to resume sex until the wound had healed, which in 93% of male subjects was within 6 weeks of circumcision[[8](#_ENREF_8)].

### **Summary of Studies**

These studies indicate that HIV+ men can undergo surgical circumcision with minimal risk. While there are limited data on those with advanced disease or very reduced CD4 the overall findings are reassuring. Given that PrePex in HIV negative men demonstrates excellent comparability to surgical VMMC, a strong argument can be made to test the safety for PrePex among HIV+ men who are above or below CD4 of 350.

**B. RESEARCH PROCEDURES INVOLVED.**

1. Provide a complete description of: a. the study design, and b. sequence and timing of all study procedures that will be performed, e.g., volume of blood, size of biopsy, drug administration, questionnaire, name of psychological test. Provide this information for each phase of the study (pilot, screening, intervention and follow-up). **Use lay language**. Attach study flow sheet, if available.

- - 1. **Study Design**

This is a one arm, open label, prospective cohort study to assess the safety and acceptability of PrePex™ device circumcision when performed by trained PrePex™ MC Providers in a HIV infected male population. The study will involve 400 HIV+ men. The estimated study timeline of 18 months is:

| **Month** | **1** | **2** | **3** | **4** | **5** | **6** | **7** | **8** | **9** | **10** | **11** | **12** | **13** | **14** | **15** | **16** | **17** | **18** |
| --- | --- | --- | --- | --- | --- | --- | --- | --- | --- | --- | --- | --- | --- | --- | --- | --- | --- | --- |
| **Study Phase** | **Start-up** | | | **Recruitment** | | | | | | **Patient Follow-Up** | | | **Analysis and Report Writing** | | | | | |

The study will have two study components which will be concurrently implemented in an estimated period of 12-18 months. Clinicians and staff involved in the study will follow the standard operating procedures of the study (SOP): Appendix 3.

1. Clinical Component

PrePex™ devices will be applied and removed by trained operators (nurses/doctors) and participants will be followed up over multiple review visits (Procedures and Schedule) to collect data on the clinical adverse events, pain, and time to complete healing. We will compare the rates of AEs among HIV+ men with PrePex MC to the lower historical proportion of men who experience an AE with surgical MC of 2.0% as seen in Kenya [[22](#_ENREF_22)] and not to the higher rates of AEs of around 3% as seen in both Uganda [[23](#_ENREF_23)] and South Africa [[24](#_ENREF_24)]. Additionally, we will qualitatively compare this data to those collected in Zimbabwe from two previous studies and routine surveillance in Zimbabwe: 1. a comparison group of HIV-uninfected men who were recently circumcised by the same MC providers using the PrePex device; 2. a comparison group of HIV-uninfected men who recently underwent routine VMMC by MC providers using the forceps-guided method.

1. Psychosocial Component

Individual interviews will be conducted by trained psychosocial interviewers to collect data from HIV-infected participants on satisfaction with the PrePex™ MC procedure, attitudes towards MC, compliance with instructions to refrain from sexual intercourse for 7 weeks post placement [(Day 49 or 6 weeks post removal) or until a clinician tells them that they are fully healed – whichever is later], barriers and motivators to uptake of VMMC through PrePex™, opinions around convenience of the device, tolerance of potential odour and whether participants would recommend PrePex™ MC to others. The interviews with same participants will be held at three points in time: prior to the procedure, two weeks post-procedure, and 90 days post-procedure (Appendices 6-8). In addition all health care providers at facilities where PrePex™ circumcision is offered will be interviewed on the acceptability of the PrePex™ procedure for HIV-infected clients. Interviews with providers (Appendix 9) will take place at one time point approximately 4 weeks post study initiation.

**Study Setting**

The PrePex device procedure will be performed by the same set of nurses/doctors at two sites. Follow-up visits may also occur in participants’ homes if the patient fails to return for the scheduled visit on Day 7, removal visit.

- Chitungwiza Hospital: This site will be set up as a new training centre to increase country capacity to train trainers of PrePex™ operators and assistants.
- Zengesa clinic in Chitungwiza: This is an established site that provides surgical VMMC
- Recruitment only sites: Opportunistic infection clinics at Beatrice and Wilkins hospitals. Recruiting scripts will be followed (Appendix 10)

**Study Duration:**

The study may last up to 18 months. Participants will be followed for 8 weeks to allow for an assessment of time until complete wound healing. or until declared fully healed by a clinician, whichever is later. Men selected for interviews will also have a visit 90 days after the MC procedure.

- - 1. **Sequence and Timing of Study Procedures:**

All study procedures will be implemented in 12-18 months as shown in the schedule (Table 1) and will include weekly review visits to assess AEs and time to complete healing.

**Procedures and Schedule**

The study schedule of events is summarized in Table 1. Each participant will undergo a series of study visits including the screening visit, device application visit, device and foreskin removal visit and additional follow-up visits up to 8 weeks. Below is a detailed description of the visits.

**Screening Visit**

- Administer informed consent (Appendix 1)
- Rapid HIV test: to assess HIV status as an eligibility criterion
- Case Report Forms (CRFs) (Appendix 4) completed by clinician which includes:
  - Clinical exam
  - Medical History
  - Current medications
  - Finger prick for blood drop collection for CD4 count by PIMA Point of Care CD4 machine (if HIV positive)

**Device Placement: Day 0**

- Client Interviews
- Case Report Forms (CRFs) (Appendix 5) completed by clinician which includes:
  - PrePex™ sizing
  - Procedural notes
  - Occurrence of any adverse events
  - Evaluation of initial patient pain level after device application
  - Hygiene instructions for penis care during device wearing period (Appendix 15)

The procedure will be carried out in a clean non-sterile environment. The subject will undergo sizing of the penis sulcus with the PrePex™ Sizing Plate. The penis will be cleaned by red Providine-Iodine solution or other disinfection solution (Chlorahexidine,etc.) with the foreskin stretched backwards to expose the inner skin for the disinfection solution. Then the foreskin will be dried with a dry gauze. The Operator will then mark the circumcision line with a clean skin marker and then the Assistant will open the corresponding sized package of the PrePex™ device, and will load the Elastic Ring on to the Placement Ring. Then, Lidocane 5% dermal cream will be applied on the inner foreskin. The Placement Ring with the Elastic Ring will be placed on the penis shaft and the foreskin tip will be stretched open to the sides by the operator hands, the operator may select to use dry gauze to affirm the grip. Then, the Inner Ring will be applied through the stretched foreskin and over the glans penis (hereinafter, "glans") so that it will be placed fixed over the sulcus behind the glans (the base of the glans). At this point, the foreskin around the inner ring is held tight by the Assistant, and the Placement Ring and Elastic-Ring are approximated to the Inner Ring by the Operator. The foreskin is then adjusted to fit the circumcision marking line to the Elastic-Ring. Then, the Elastic-Ring is released from the Placement Ring on to the Inner Ring groove, initiating homeostasis. The procedure is then completed. Medication based on 400mg Ibuprofen is given to the subject to use at home if needed (or Paracetamol [Tylenol] if Ibuprofen is not appropriate for the patient). The subject will then take part in a formal discharge session in a class room, where he will be instructed to return for a follow up visit and in any non-sustained situation and to take painkillers in case of pain. If an infection is identified at any of the follow-up visits, patients may be treated with the antibiotics Cloxacillin or Ciprofloxacin. All patients will be given oral instructions for hygiene in Prepex post insertion care, adapting the device instructions for the local context (Appendix 15).

**Day 7** : **Device removal**

- The PrePex™ device is removed
- Dead skin is removed using sterile scissors
- Sterile gauze and adhesive tape will be applied to the wound
- Case Report Forms (CRFs) (Appendix 5) completed by clinician which includes:
  - Clinical exam
  - Evaluation of patient pain level during and after device removal
  - Occurrence of any adverse events
  - Current Medications
  - Photograph of the penis taken if consent granted
  - Reminders to abstain from sexual intercourse and masturbation
- Preparation and procedure time may be measured by stopwatch

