**The Primary Objectives are**:

- 1. To assess the safety of the PrePex™ device when applied to HIV positive men by assessing the rate of the clinical adverse events.

1. **The Secondary Objectives are:**
   1. To assess the level of care required to provide PrePex™ MC to HIV positive men, when taking into account the following parameters:
      1. PrePex™ procedure duration (a combination of the application and removal procedure times)
      2. Pain management at different stages of the procedure
      3. Time to complete healing, defined as, intact epithelium (unbroken skin) covering the epithelial as judged by the provider on visual inspection, meaning that none of the following are present: sutures, scabbing, drainage, moisture, gaps between epithelial edges or ulceration.]
   2. To evaluate the acceptability of the PrePex™ procedure to HIV-positive men as well as service providers.
   3. To evaluate Facilitators/Barriers for seeking VMMC among HIV-infected men
   4. To assess compliance with instructions to refrain from sexual intercourse until seven weeks post-placement-- Day 49 post-placement visit (6 weeks post-removal) or as instructed by a clinician, whichever is later, as a public health safety issue.
   5. Assess AE monitoring and reporting systems with respect to completeness and timeliness of reporting

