Zimbabwe has piloted the PrePex device in a series of clinical trials since October 2011. The PrePex™ MC device was developed and manufactured in Israel by CircMedTech. It does not require local anaesthesia and is bloodless. The device’s circumcision mechanism is based on controlled necrosis of the foreskin over a one-week period. The PrePex**^TM^** device was assessed in Zimbabwe in a three phase trial which included clinical and psychosocial objectives. The three phase clinical trial of the “PrePexTM” Device for use in scaling up male circumcision (MC) in Zimbabwe started on 24th October, 2011 at Spilhaus centre in Harare. Studies in Phase I and Phase II of the trial (Protocol # MRCZ/A/1628), have established the safety and efficacy of PrePexTM among HIV-negative men, and the ongoing Phase III trial is trying to establish the safety and efficacy of task shifting PrePex circumcision from doctors to nurses for those populations. The previous trials included: 1) a Safety phase to determine the safety of the PrePex**^TM^** device among HIV+ men; 2) a Comparative phase to assess its performance compared directly to surgical MCs; and 3) a Field Study phase to assess the ease of use among trained nurses or general practitioners in an implementation roll out in District Hospitals rather than at the centrally located MC Centre. The findings from these three trials have since established the safety and efficacy of the PrePex™ device, and allowed Zimbabwe’s MOHCC to present reports to WHO for pre-qualification approval of the PrePex™ device. Currently, the WHO has pre-qualified PrePex for HIV-negative men. Zimbabwe has since obtained WHO pre-qualification to use the PrePex™ device for circumcision of HIV-negative adult men.

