**Day 9**

- The dressings on the wound are removed
- Case Report Forms (CRFs) (Appendix 5) completed by clinician which includes:
  - Clinical exam
  - Evaluation of patient pain level
  - Occurrence of any adverse events
  - Current Medications
  - Photograph of the penis taken if consent granted
  - Reminders to abstain from sexual intercourse

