**Table 1: Study timeline**

| **Table 1: Protocol Description and Timing of Assessments** | | | | | | | | |
| --- | --- | --- | --- | --- | --- | --- | --- | --- |
|  | **Screening and Recruitment Visit** | **Application Visit** | **Removal Visit** | **Physical Examination of the genital Visit** | **Physical Examination of the genital Visit** | **Physical Examination of the genital Visit** | **Physical Examination of the genital Visit** | **Physical Examination of the genital Visit** |
| **Visit #** | **1** | **2** | **4** | **5** | **6** | **7** | **8** | **9, 10, 11, 12, 13** |
| **Day (D)/week (w)** | **–7 to D0** | **D0** | **D7** | **D9** | **D14** | **D21** | **D28** | **D35, 42, 49, 56, 63** |
| Informed consent | X |  |  |  |  |  |  |  |
| Screen with Inclusion/exclusion criteria | X |  |  |  |  |  |  |  |
| Participant specimen collection for CD4 count | X |  |  |  |  |  |  |  |
| Medical history & Demography | X |  |  |  |  |  |  |  |
| Current medication including pain killers | X | X | X | X | X | X | X | X |
| Psychosocial interview |  | X |  |  | X |  |  | X (D90) |
| Genital examination and potential pictures | X | X | X | X | X | X | X | X |
| Video procedure |  | X | X |  |  |  |  |  |
| Device application |  | X |  |  |  |  |  |  |
| Foreskin removal |  |  | X |  |  |  |  |  |
| Device removal |  |  | X |  |  |  |  |  |
| Subject's subjective pain, tingling and discomfort evaluation (VAS score) |  | X | X | X | X | X | X | X |
| Evaluate side effects and AE |  | X | X | X | X | X | X | X |
| Statistical analysis of data |  |  |  |  |  |  |  | Interim safety report |

2. Would subjects undergo these or similar procedures (medical, psychological, educational, etc.) if they were not taking part in this research?  No  Yes If “Yes,” describe how the study procedures differ from what subjects would otherwise undergo.

HIV+ men are not excluded from VMMC according to the Zimbabwe MOHCC, but the program is intended as an HIV prevention program and focuses on HIV-negative men. The PrePex™ device was approved by the Zimbabwe MOHCC for use among HIV-negative men ages 18 and older, and routine implementation began in early 2014. This protocol follows the standard protocols for this activity, extending the target group to include HIV-positive men. Men participating in this study are currently eligible for forceps-guided MC. As with all MOHCC VMMC program services, participants in the study will also receive VMMC at no cost.

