a. Name of the device: PrePex™

The PrePex™ device is FDA cleared with 510(k) status (K103695; see 510(k) and is thus not considered “investigational”; however we are providing the following details for the information of the IRB review committee. The device is certified CE Mark Class IIa. It is manufactured using USP Class VI biocompatible elastomeric materials compliant to ISO_13485 Medical Devices (Quality Management systems) and FDA, 21 CFR177. 2600. Circ MedTech is ISO 13485 certified.

b. Name of the manufacturer: Circ MedTech

c. Description of its purpose and how you will use it in this study:

PrePex™is a single use, disposable device; indicated for circumcision of adult men, defined as circumferential excision of the foreskin or prepuce at or near the level of coronal sulcus, with minimal amount of preputial skin remaining.

d. Descriptions of previous studies in humans and animals:

The WHO Technical Advisory Group (TAG) on Innovations in Male Circumcision reviewed eight studies from 3 African countries in the WHO Framework for Clinical Evaluation of Devices (see WHO Pre-Qualification Report: <http://www.who.int/diagnostics_laboratory/male_circumcision/130530_pqmc_public_report_final_v1.pdf>). All studies included only healthy males 18 years and older. The device was placed successfully on 2417 eligible men. Adverse events occurred among 1.7% of participants; the majority were Mild and Moderate, while 0.4% were considered Serious as prompt surgical intervention was required to prevent serious long-term sequelae (in all cases surgical intervention was successful with no complications and satisfactory outcomes). The AE rate was lower among men who had PrePex™ circumcision than among men who had conventional surgery, but this difference was not statistically significant. No mechanical failures were reported. Healing time appears to be about 1 – 2 weeks longer than following conventional surgical circumcision. Some pain occurs with PrePex™ procedures, primarily during the first few days after placement and briefly on removal of the device. Complaints of unpleasant odor were also noted by some study participants and providers.

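### No pain score is scheduled for Days 1–6 of device wear, the period in which the protocol itself places most of the pain

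*Protocol*

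**What the plan says.** The secondary objectives in Protocol Section IX make "Pain management at different stages of the procedure" one of three parameters for the level of care that HIV-positive men need. The clinical component in Section B says that men are followed "to collect data on the clinical adverse events, pain, and time to complete healing". The data collection overview in Section D assigns the level-of-care objective to all 400 men, with the case report form (CRF) as the tool.

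The Background describes the device mechanism as "controlled necrosis of the foreskin over a one-week period", so wear runs from Day 0 to Day 7. The visit descriptions in Section B fix when pain is scored:

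- Day 0: "Evaluation of initial patient pain level after device application"
- Day 7: "Evaluation of patient pain level during and after device removal"
- Day 9: "Evaluation of patient pain level", repeated at Day 14 and at each later visit except Day 90

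Table 1 agrees. Its VAS row is marked at D0, D7, D9, D14, D21, D28 and D35 to D63. There is no column between D0 and D7, and no recall period is given.

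On timing, the summary of previous studies in Section J reports that pain occurs "primarily during the first few days after placement and briefly on removal of the device".

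**The concern.** The schedule does not match the protocol's own account of when pain occurs. Removal, described as a brief source of pain, is scored twice. The first days after placement, described as the main source, are covered only by an initial reading taken once the device is on. During those days the men are at home with an analgesic to use as they see fit, and no scheduled contact takes place.

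A by-stage pain summary built from these data would cover application, removal and recovery but leave out wear. The findings are meant to inform roll-out, clinician training and counselling before the procedure. A summary without the wear stage could understate the pain that men manage on their own and the support they need. This is a matter of data capture, so it cannot be left to the analysis plan.

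**Working it through.** No sample size, power or error rate bears on this point. The check sets the scheduled scores beside the protocol's statement on timing.

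| Period | Scheduled pain scores | Source | Section J on pain |
| --- | --- | --- | --- |
| Day 0, after application | 1 (initial) | Day 0 list; Table 1 | Start of the main period |
| Days 1–6, device on, at home | 0 | No visit in the text or in Table 1 | Contains the first few days, the main period |
| Day 7, removal | 2 (during and after) | Day 7 list; Table 1 | Brief pain |
| D9, D14, D21, D28, D35, D42, D49, D56, D63 | 1 per visit attended, up to 9 (D56 and D63 depend on healing) | Later visit lists; Table 1 | Not named |

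1. Size of the gap. Six days per man without a scheduled score, over 400 men, is 6 × 400 = 2,400 man-days of wear. The first few of those six days are the ones that Section J singles out.

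2. Could the Day 7 score cover the wear period? The Day 7 list ties it to removal. The Day 7 mark in the Table 1 VAS row carries no such limit, but it states no recall window either. Neither place asks a man about the days before the visit.

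3. Could other records fill the gap?
   - Medication: painkillers are recorded as current medication at each visit, Day 7 included. This is not a pain intensity, and the text does not ask for total use since placement.
   - Adverse events: these are recorded at Day 7 and pain is a listed risk, so severe wear-stage pain has a route into the data. Pain below the threshold of an adverse event does not.
   - Unscheduled visits: men are told to return for severe or worsening pain. This depends on the man coming in.
   - Day 14 interview: at most 103 men are selected, so it could not supply a score for all 400.

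4. Result. For Days 1–6 no scheduled item described in the protocol gives a graded pain score for every man.

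**The case against.** The strongest objection concerns the meaning of the objective. It speaks of pain management and of stages of the procedure, and the neighbouring parameter defines procedure duration as application plus removal. Read that way, the scored stages are the stages of the procedure, and painkiller use is tracked at every visit. This reading is possible, but the device works by being worn for a week, and Section B lists pain itself among the data to be collected. A stage summary without wear would still omit the period that the protocol calls the main one.

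A second objection is that the CRF (Appendix 5), the operating procedures (Appendix 3) and the two-week questionnaire (Appendix 7) are not shown, and that the Day 7 list is not stated to be exhaustive. A recall item may exist, and this part of the objection stands. What the protocol itself says about the Day 7 pain item is nevertheless limited to removal.

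Four stronger inferences should be resisted:

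- That the peak of pain is missed. Section J says when pain mainly occurs, not when it is most intense, and removal, the other period it names, is scored.
- That none of the seven days of wear has a score. The Day 0 score is taken with the device in place, so the exact statement is that Days 1–6 have none.
- That severe wear-stage pain would be invisible. Adverse event and painkiller recording at Day 7, together with unscheduled visits, give it a route.
- That the jump from visit 2 to visit 4 in Table 1 points to a dropped pain visit. It shows only a numbering slip.

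**Conclusion.** The point holds in this form: pain is scored at application, at removal and after removal, but no score is scheduled for Days 1–6, the part of wear that contains most of the period Section J names as the main one for pain. What is lost is a graded wear-stage score for each of up to 400 men. Severe pain and some analgesic use may still be recorded by other routes.

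The weight is moderate. Pain is one of three parameters under one secondary objective, and no primary safety conclusion turns on a VAS score. The change is still worth making because the missing data cannot be recovered later and the remedy is cheap. The conclusion assumes that the CRF follows the protocol's description of it and that the Section J statement on timing also applies to HIV-positive men, for whom the protocol gives no separate pain data.

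**What to change.** In the Day 7 visit description and the Table 1 VAS row, add three items to the Day 7 CRF, completed for every man before removal starts:

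1. worst VAS since placement, by recall;
2. VAS now, with the device in place;
3. analgesic use since placement, as number of days and number of tablets.

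Report pain by stage as application, wear, removal and post-removal. If Appendix 5 already holds such an item, it is enough to name it in the protocol and state its recall period. The Table 1 visit numbering can be tidied at the same time as a separate editorial matter.

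The cost is three form fields at an existing visit, with no added visit, and no change to treatment. The yield is up to 400 wear-stage scores. There are two limits. Worst pain is recalled over about seven days. The item also covers only men who attend the removal visit, and the protocol plans for some who miss it.
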